### Trial intervention

#### Liberal group

Participants allocated to the liberal oxygenation group will receive supplemental oxygen and ventilator settings at the discretion of the treating clinical team with the aim of maintaining peripheral oxygen saturations >94%. This will be continued until all ventilator support (delivered invasively or non-invasively) has been discontinued during this PICU admission. All other care (including antimicrobial therapy, fluid therapy, analgesic and sedative agents and bronchodilator therapy) will be determined by the clinical team primarily responsible for the participant’s care.

#### Conservative group

Participants allocated to the conservative oxygenation group will receive supplemental oxygen and ventilator settings at the discretion of the treating clinical team with the aim of maintaining peripheral oxygen saturations between 88% and 92% (inclusive). This will be continued until all ventilator support (delivered invasively or non-invasively) has been discontinued during this PICU admission. All other care will be determined by the clinical team primarily responsible for the participant’s care.

### Data collection and follow-up

Detailed guidance for the collection of data will be provided in the trial-specific standard operating procedure. All data items will be objectively defined according to relevant national and international guidelines. Data will be collected at baseline prior to randomisation, daily and at discharge from PICU as detailed in table 1. Patients will be followed-up until discharge from a participating PICU. Data entered onto the secure trial database will undergo validation checks for completeness, accuracy and consistency of data. Queries on incomplete, inaccurate or inconsistent data will be sent to the research team at participating sites for resolution.

**Table 1 T1:** Data collection time points for enrolled participants

Time point		
Baseline	Daily	PICU discharge
Age	Ventilation mode*	Date of discharge
Gender	Interventions for organ support†	Survival status
Weight	Hourly SpO_2_ values‡	Discharge diagnosis
Acute diagnosis	–	–
Chronic diagnosis	–	–
Severity of gas exchange	–	–
Cause of respiratory failure	–	–
PIM2r score	–	–

*Ventilation mode including FiO_2_ and mean airway pressure.

†Including use of vasoactive drugs, ECMO, blood transfusion, renal support and neuromuscular blocker or sedative drug infusions.

‡Hourly SpO_2_ values for first 24 hours, then 4 hourly until day 6 postrandomisation and 12 hourly thereafter until the end of mechanical ventilation.

ECMO, extracorporeal membrane oxygenation; FiO_2_, fraction of inspired oxygen; PICU, paediatric intensive care unit; PIM2r, paediatric index of mortality 2 recalibated; SpO_2_, peripheral oxygen saturations.

### Sample collection

Samples of blood and urine will be collected to assess for possible mechanisms of oxidative injury. Blood from indwelling invasive lines will be sampled within 24 hours of randomisation and again up to 72 hours postrandomisation (or immediately prior to removal of suitable invasive sampling lines in patients with an anticipated shorter length of stay). Plasma from samples of 1–1.5 mL of whole blood will be analysed for malondialdehyde, ischaemia-modified albumin and total antioxidant status. Leucocyte hypoxia-inducible factor-1 alpha mRNA expression will also be estimated. Other markers of plasma and leucocyte oxidative stress may be investigated. Urine samples will also be taken at the same time points (within 24 hours and up to 72 hours postrandomisation) to discover biomarkers of oxidative stress using metabolomics and proteomic analyses.

### Adverse events

All infants and children eligible for Oxy-PICU are critically ill and due to the complexity of their condition are at increased risk of experiencing AEs. Many of these events are expected as a result of the infant/child’s medical condition and standard treatment received in the PICU and may not be related to participation in the trial. Consequently, any AEs occurring as a result of the infant/child’s medical condition or standard critical care treatment will not be reported. Pre-existing conditions do not qualify as AEs unless they worsen but should be documented in the infant/child’s medical notes. AEs that occur between randomisation and PICU discharge must be recorded in the participant’s medical notes and on the Oxy-PICU case report form. Those meeting the definition of a serious AE (SAE) must, in addition, be recorded in the SAE log and reported to the Intensive Care National Audit & Research Centre (ICNARC) Clinical Trials Unit (CTU), using the trial specific Oxy-PICU SAE Reporting Form, by fax within 24 hours of observing or learning of the SAE.

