## Abstract

**Introduction:**

Optimal targets for systemic oxygenation in paediatric critical illness are unknown. Observational data indicate that high levels of arterial oxygenation are associated with poor outcomes in resuscitation of the newborn and in adult critical illness. Within paediatric intensive care units (PICUs), staff prevent severe hypoxia wherever possible, but beyond this there is no consensus. Practice varies widely with age, diagnosis, treating doctor and local or national guidelines followed, though peripheral blood oxygen saturations (SpO_2_) of >95% are often targeted. The overall aim of this pilot study is to determine the feasibility of performing a randomised trial in critically ill children comparing current practice of liberal SpO_2_ targets with a more conservative target.

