### Study aim

The overall aim of this study is to determine if it is feasible to perform a safe, adequately powered and affordable definitive randomised controlled trial in critically ill children comparing current practice of liberal targets for systemic oxygen levels with more conservative targets. The underlying hypothesis of a definitive trial is that the harm of interventions to raise arterial oxygen saturation to >94% exceeds the benefits of these interventions.

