## Methods and analysis

### Study design and setting

Oxy-PICU is a pragmatic, open, pilot randomised controlled trial in infants and children accepted for emergency admission to participating PICUs. Study recruitment will be at three PICUs and their local PICU transport teams representing typical configurations for UK PICUs (general or combined ICUs in general academic medical centres or within stand-alone children’s hospitals).

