### Outcome measures

As this is a pilot study outcome measures for the study will be focused on assessing the study feasibility for a larger scale definitive study as noted in box below.BoxOutcome measures of the Oxy-PICU feasibility study**Primary outcome measure**Number of eligible patients recruited per site per month.**Secondary outcome measures**Proportion of parents/legal representatives refusing deferred consent.Proportion of eligible patients randomised (target 50%).Distribution of time to randomisation.Proportion of systemic oxygen saturations within the target range in each group.Proportion of patients in each arm requiring other treatments influencing tissue oxygen delivery (blood transfusion and inotropic support).Characteristics and completeness of potential primary endpoints for a definitive study including: length of ventilation, length of paediatric intensive care unit (PICU) stay, PICU mortality and days of organ specific support.Observed adverse events.Time taken for data collection and entry.Distribution of markers of ischaemia and antioxidant status.

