## Discussion

We believe that there is an urgent need for high-quality clinical evidence to inform on the optimal targets of systemic oxygenation during paediatric critical illness. Inferences ‘up’ from extremely premature infants or ‘down’ from adults are in conflict and unlikely to be valid in children because of age-related differences in the acute physiological responses to hypoxia/hyperoxia and distinct comorbidities.

A clinical trial comparing current (liberal) targets for systemic oxygenation with lower (conservative) targets in critically ill children is therefore required. This pilot study is a crucial step to understand if this is possible and also affords the opportunity to learn more about the biological mechanisms underlying costs and benefits of oxygen therapy in children.

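### The adverse-event rule filters events by judged cause in an open trial whose comparator is current practice, and it is not reconciled with the instruction to record all events on the case report form

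*Protocol article*

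**What the plan says.** Two instructions stand in the same section, Adverse events. The first is an exclusion by cause: "any AEs occurring as a result of the infant/child’s medical condition or standard critical care treatment will not be reported". The second is a recording duty with no mention of cause: "AEs that occur between randomisation and PICU discharge must be recorded in the participant’s medical notes and on the Oxy-PICU case report form". Events that meet the serious definition must also be logged and sent to the trials unit within 24 hours. The section does not say whether the exclusion applies before the case report form is filled in or only to what is passed on afterwards.

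Other sections show why this matters:

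- **Blinding.** Study design and setting: "Oxy-PICU is a pragmatic, open, pilot randomised controlled trial".
- **Comparator.** The liberal target is described as what is done now in three places: the Abstract ("comparing current practice of liberal SpO_2_ targets with a more conservative target"), Study aim ("comparing current practice of liberal targets for systemic oxygen levels with more conservative targets") and the Discussion ("comparing current (liberal) targets for systemic oxygenation with lower (conservative) targets").
- **Use of the data.** The Outcome measures box lists "Observed adverse events" as a secondary outcome. Study objectives include testing follow-up for adverse-event reporting. Trial monitoring and oversight gives safety monitoring to the data monitoring committee, which advises on continuation.

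**The concern.** Whether an event is reported turns on a judgement about its cause, made by people who can know the allocation. In a trial where one arm is close to usual care, that judgement need not work the same way in both arms. Harm that follows the pursuit of a higher saturation can be seen as a consequence of standard critical care and left out. The same event under the conservative target is a departure from usual practice and is more readily linked to the trial. In the other direction, harm from lower oxygenation in a ventilated child with abnormal gas exchange can look like the illness itself, and so be left out of the conservative arm.

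Study aim states the hypothesis that the harms of raising saturation above 94% outweigh the benefits. The harms of interest in the liberal arm are thus among those the exclusion can remove. A pilot that is meant to test adverse-event reporting would also hand the same rule on to the definitive trial.

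**Working it through.** The documents give no adverse-event rate and no attribution share, so there is no figure to reproduce. The check is mainly textual.

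**Step 1: two readings of the Adverse events section.**

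- *Narrow reading.* Recording means the notes and the case report form, and reporting means passing events on. The form then holds all events in both arms, and the exclusion affects only what goes further.
- *Broad reading.* Events judged to come from the illness or standard care are dropped altogether. The form then holds only the remainder, and the secondary outcome is a count of events that survived a causal judgement.

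The section's own usage gives the narrow reading some support, because the recording sentence concerns notes and form while the reporting route is the one for serious events. The exclusion, however, covers any adverse event and states no limit to onward reporting. Both readings are open to a site.

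**Step 2: can attribution differ by arm?** The rule is worded identically for both arms, so any asymmetry must come through its application. The conditions for that are present: allocation is open, no blinded attribution is described, and one arm is called current practice.

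**Step 3: what the filter can do under the broad reading.** Inputs from the protocol are the target of 120 participants (Abstract) and 1:1 allocation (Screening and randomisation), so n = 120 / 2 = 60 per arm. True risks and reporting shares below are assumptions.

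Expected reported count = n × true risk × share reported.

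| True events, liberal v conservative | Share reported, liberal v conservative | Expected reported |
|---|---|---|
| 60 × 0.20 = 12 v 12 | 50% v 50% | 6 v 6 |
| 12 v 12 | 25% v 75% | 3 v 9 |
| 12 v 12 | 75% v 25% | 9 v 3 |
| 60 × 0.15 = 9 v 60 × 0.30 = 18 | 0% v 0% | 0 v 0 |

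With shares of 25% v 75%, the reported counts run from 1.5 v 4.5 at a true risk of 10% to 4.5 v 13.5 at 30%. Rows two and three have the same truth and opposite apparent differences. Row four hides a true doubling. Equal shares (row one) preserve equality. The table shows only that direction and size depend on shares that nobody will know. It does not estimate them.

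**The case against.** A reader might infer that liberal-arm harm is standard care by definition, so that safety data are bound to be filtered differently by arm. The documents do not support this. The Trial intervention section lists the liberal target as an allocated intervention. The section on care before and after randomisation separates care directed at the trial saturation target from all other care, in both groups. On that reading, harm from pursuing either target is trial-related. The Introduction also says that practice varies widely. Differential attribution is therefore a risk, not a certainty. This objection stands.

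Four further points have weight:

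- If the narrow reading is right, the case report form already holds the events, and most of the loss disappears. This stands as a possibility, but the text does not settle it.
- The Statistical analysis section does not list adverse events among the outcomes compared by group, and the strengths and limitations summary treats clinical outcomes as hypothesis-generating. This stands and lowers the stakes.
- Mortality, ventilation settings, organ support, transfusion and serial SpO2 are collected in both arms with no attribution test, and nothing confines the data monitoring committee to adverse-event reports. This stands as a partial safeguard. These items do not replace the adverse-event outcome.
- The article is condensed, and event lists or causality procedures may sit in the full protocol. Their absence here is accordingly no criticism. The point rests on a rule that the article does state.

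Restricting adverse-event reporting in critical illness is reasonable in itself, since many events are expected. The difficulty lies in restricting by judged cause in an open trial.

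**Conclusion.** The point holds in a limited form. The two instructions are unreconciled, and nothing in the article removes the causal filter. If sites apply it before recording, the adverse-event outcome depends on open attribution and can be biased in either direction. A reader might conclude that the bias runs against the conservative arm, or attach a probability of a false difference to it. Neither follows: the direction depends on which harms staff ascribe to what, no event rates are given, and no test of adverse events is planned.

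The conclusion assumes that sites could take the broad reading and that the full protocol does not already resolve it. Given the unfiltered outcomes and the descriptive purpose of the pilot, this is a cheap improvement and not an essential correction. It is best made before recruitment, because events that were not recorded at the time cannot be recovered reliably in the analysis.

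**What to change.** 1. Reconcile the two sentences in the Adverse events section, so that the exclusion limits only expedited or onward reporting and does not affect what is entered on the case report form.
2. State that, for attribution, care aimed at either SpO2 target counts as trial intervention.
3. Prespecify a short list of events plausibly related to oxygenation or ventilation. Record them on the form in both arms from randomisation to PICU discharge whatever the judged cause, and summarise them by arm. If the full protocol already has such a list, refer to it.
4. Keep causality assessment for expedited reporting of serious events.

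The cost is a few items on the form, a sentence or two of protocol text and slightly more data entry.

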### Trial monitoring and oversight

The ICNARC CTU will conduct at least one monitoring visit to participating sites during the course of the pilot study. The trial will be supervised by the Trial Steering Committee (TSC), which will be chaired by an independent member and will include at least two additional independent members and a service user representative.

Safety will be monitored by the Data Monitoring and Ethics Committee (DMEC) throughout the trial period. All members of the DMEC will be independent of both the Oxy-PICU Trial Management Group and the TSC. The DMEC will operate under the DAMOCLES Charter^17 18^ and will report to the TSC, making recommendations on the continuation, or not, of the trial. The ICNARC CTU will be responsible for the day-to-day management of the trial and will act as custodian of the data. The ICNARC CTU will ensure that all SAEs are reported, as appropriate, to the REC.

### Outcome measures

As this is a pilot study outcome measures for the study will be focused on assessing the study feasibility for a larger scale definitive study as noted in box below.BoxOutcome measures of the Oxy-PICU feasibility study**Primary outcome measure**Number of eligible patients recruited per site per month.**Secondary outcome measures**Proportion of parents/legal representatives refusing deferred consent.Proportion of eligible patients randomised (target 50%).Distribution of time to randomisation.Proportion of systemic oxygen saturations within the target range in each group.Proportion of patients in each arm requiring other treatments influencing tissue oxygen delivery (blood transfusion and inotropic support).Characteristics and completeness of potential primary endpoints for a definitive study including: length of ventilation, length of paediatric intensive care unit (PICU) stay, PICU mortality and days of organ specific support.Observed adverse events.Time taken for data collection and entry.Distribution of markers of ischaemia and antioxidant status.

### Statistics

#### Power calculation

The Oxy-PICU pilot study is primarily set-up to test the feasibility of the protocol to recruit eligible patients. Therefore, there is no primary outcome to be compared between the two groups and, hence, a usual power calculation to determine sample size is not appropriate. Instead, the sample size has been determined to be adequate to estimate critical parameters to be tested to a necessary degree of precision. Based on available data from PICANet, it is anticipated that the participating sites will recruit approximately 4–10 children per month, providing a total of approximately 120 children in 6 months.

#### Statistical analysis

Descriptive analysis will be conducted to assess the objectives of Oxy-PICU. All analyses will be carried out on an intention-to-treat basis. Screening data will be reported by site and randomisation, and consent data will be reported by site and treatment group. Baseline demographic and clinical data as detailed in table 1 will be summarised by group and overall. Continuous variables will be summarised as mean (SD) and median (IQR) while categorical variables will be summarised as number (percentage).

Adherence to the intervention will be reported as:Time in SpO_2_ target range (hours) – mean (SD) and median (IQR) will be reported by treatment group.Percentage of time points SpO_2_ measurements in range by treatment group.

Daily organ support procedures will be presented graphically by plotting the percentage of patients in each group receiving each recorded support procedure. Daily interventions received will be presented graphically by plotting the mean (SD) of each intervention.

A comparison of outcomes by treatment group will be reported for the following outcome measures:Length of PICU stay.Length of IV.Length of NIV.Ventilator-free days at day 30.Duration of organ support.PICU mortality.

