### Study objectives

To test the willingness of clinicians to screen, recruit and randomise eligible patients.To estimate the recruitment rate.To test, following randomisation, delivery of and adherence to, the intervention and demonstrate separation between the groups.To test acceptability of the deferred consenting procedures and participant information.To test follow-up for the identified, potential, patient-centred primary and other important secondary outcome measures and for adverse event (AE) reporting.To inform final selection of a patient-centred primary outcome measure.To estimate the characteristics (eg, SD) of the selected patient-centred primary outcome measure to inform sample size estimation.To inform content and time needed for final data collection.To investigate the feasibility of collecting samples suitable for estimation of ischaemic/oxidative injury and antioxidant status.

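### Neither stated adherence measure estimates the share of intervention time on target: hours in range scale with ventilated time, and the percentage of readings over-weights the first 24 hours

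*Protocol article*

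**What the plan says.** The Statistical analysis section names two adherence summaries. The first is "Time in SpO_2_ target range (hours) – mean (SD) and median (IQR) will be reported by treatment group". The second is "Percentage of time points SpO_2_ measurements in range by treatment group". The Outcome measures box carries a related secondary outcome: "Proportion of systemic oxygen saturations within the target range in each group".

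The readings behind these summaries are not evenly spaced. The footnote to Table 1 (Data collection and follow-up) gives the schedule: "Hourly SpO_2_ values for first 24 hours, then 4 hourly until day 6 postrandomisation and 12 hourly thereafter until the end of mechanical ventilation".

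The period over which a child can be on target is set by ventilation. For both arms the Trial intervention section says of the target: "This will be continued until all ventilator support (delivered invasively or non-invasively) has been discontinued during this PICU admission".

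Duration of ventilation is also an outcome. The Statistical analysis section compares length of invasive and of non-invasive ventilation and ventilator-free days between arms, and the Outcome measures box lists length of ventilation among the candidate primary endpoints for the definitive trial.

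The article states no weighting of readings by the interval they represent and no ventilated-time denominator for the hours measure.

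**The concern.** One of the Study objectives is to test "delivery of and adherence to, the intervention and demonstrate separation between the groups". The natural quantity for that is the share of time under the intervention that each child spent in the allocated range.

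Hours in range are that share multiplied by ventilated time. A child who stays on the ventilator longer collects more hours at the same adherence; one who weans early or dies collects fewer. If the target itself alters ventilation time, the arms can differ in hours in range with no difference in adherence.

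The percentage of time points does not have that defect, but one reading stands for 1, 4 or 12 hours depending on when it was taken. Unweighted, an hour in the first 24 h counts 4 times as much as an hour between then and day 6, and 12 times as much as a later hour. If adherence drifts, the figure is not the share of time on target. At stake is how well the pilot can tell the definitive trial's designers whether the targets were delivered and whether the arms separated.

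**Working it through.** The plan gives no adherence figure, so there is none to reproduce.

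**Inputs from the article.** 24 readings in the first 24 h, then 6 a day to day 6, then 2 a day (Table 1 footnote). The intervention lasts until ventilator support ends (Trial intervention). I take the end of mechanical ventilation in the footnote to be the same moment, and day 6 to end at 144 h.

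**Assumed, because the article does not give them.** Ventilation durations, and the probability that a reading is in range on day 1 and later.

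**1. Hours in range.** Hours = adherence × 24 × ventilated days.
- 60% adherence, 4 days: 0.60 × 96 = 57.6 h
- 60% adherence, 6 days: 0.60 × 144 = 86.4 h, which is 50% more at the same adherence
- 80% adherence, 4 days: 0.80 × 96 = 76.8 h, below the 86.4 h of the child with 60% adherence over 6 days

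The proportionality holds whatever the time course of adherence; only the example values are assumed.

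**2. Share of readings against share of time, first 24 h.** Total readings: 3 days, 24 + 2×6 = 36; 5 days, 24 + 4×6 = 48; 6 days, 24 + 5×6 = 54; 10 days, 54 + 4×2 = 62.

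| Days ventilated | Readings | First 24 h, share of readings | First 24 h, share of time |
|---|---|---|---|
| 3 | 36 | 24/36 = 67% | 33% |
| 5 | 48 | 24/48 = 50% | 20% |
| 6 | 54 | 24/54 = 44% | 17% |
| 10 | 62 | 24/62 = 39% | 10% |

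If the 4-hourly period ends at 120 h instead, a 10-day course has 58 readings and the first 24 h supplies 24/58 = 41% of them. At 10 days (144 h reading), time after day 6 is 40% of the course but 8/62 = 13% of the readings.

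**3. Effect on the percentage, 6 ventilated days.**
- 70% on day 1, 45% later. Unweighted: (24×0.70 + 30×0.45)/54 = 30.3/54 = 56.1%. Time-weighted: (0.70 + 5×0.45)/6 = 49.2%. Gap +6.9 points.
- 40% on day 1, 65% later. Unweighted: (24×0.40 + 30×0.65)/54 = 29.1/54 = 53.9%. Time-weighted: (0.40 + 5×0.65)/6 = 60.8%. Gap −6.9 points.
- Constant adherence: the two agree exactly.

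With one level on day 1 and another afterwards, the gap is (share of readings − share of time) × (day-1 level − later level): here (0.444 − 0.167) × 0.25 = 0.069.

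At 10 days with a wider change, 40% then 70% gives 36.2/62 = 58.4% unweighted against 67.0% time-weighted; 70% then 40% gives 32/62 = 51.6% against 43.0%.

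**The case against.** **The two measures are reported together.** Turning intermittent readings into hours already requires an interval for each reading, so the numerator of a time-weighted share is in effect planned, and ventilation lengths are reported by arm elsewhere in the same section. This stands in part: a reader could form a rough arm-level ratio of means. It does not give a per-child percentage, and medians cannot be divided in this way.

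**The percentage is distorted only under assumptions.** This stands. With constant adherence there is no distortion. Both arms share one schedule, so the contrast between them moves only if time profiles or durations differ. The profiles above show sensitivity in both directions, not a demonstrated bias. The box, however, reports the proportion in each group, so each arm's level matters as well as the contrast.

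**The missing detail may sit in the analysis plan.** An unseen plan could add weighting. The point is not that detail is absent, though: the article names two measures, and as worded neither is the share of time on target.

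**Interval weighting has a cost.** After day 6 each reading would stand for 12 hours, so late estimates are noisier. This is true, and a display by period makes it visible.

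**Stronger readings that the article does not support.**
- A reader might infer that the percentage mostly describes day 1. The first 24 h supplies more than half of the readings only below 5 ventilated days, and the article gives no durations.
- A reader might infer that readings are pooled across children within an arm. The wording does not say so; a per-child percentage summarised by group is equally compatible with it.
- A reader might apply the 1.28 length-of-stay ratio from the Introduction to predict 22% fewer hours in range in the conservative arm (1/1.28 = 0.78). That ratio is for hospital stay in non-critically ill children with bronchiolitis under different targets, and says nothing about ventilation time here.

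**Conclusion.** The point holds. As worded, the two adherence measures do not estimate the share of intervention time spent in range.

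For hours in range the defect needs no assumption about how adherence changes over time: the measure is proportional to ventilated time, an outcome compared between arms. For the percentage of time points, the over-weighting of the first 24 h follows from the schedule, but its numerical effect depends on drift in adherence: about 7 points either way at 6 days for an assumed 25-point change, 8.6 points at 10 days for an assumed 30-point change, and zero if adherence is constant.

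This is a should-fix. A reader might take it as a threat to the pilot's main conclusion, but the primary outcome is recruitment per site per month. Adherence is a descriptive secondary outcome with no threshold or test attached in the article, and no sample size rests on it.

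**What to change.** For each child, compute the percentage of time from randomisation to the end of ventilator support spent in the allocated range, weighting each reading by the interval it represents. Summarise these percentages by arm as mean, SD, median and IQR, and tie the secondary outcome in the box to this definition.

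Show hours in range only beside total ventilated hours over the same window.

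Give the percentage in range separately for the first 24 h, from then to day 6, and after day 6. Within a period the sampling interval is constant, so drift in adherence and the thinness of the late data can both be seen.

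The cost is a sentence in the Statistical analysis section and a few lines of code. No additional data are needed. The one drawback is the noisier late estimate from 12-hourly readings.
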